### Study Instruments

A mixed-method approach will be used to capture the innovation process of project implementation. Qualitative methods will be sought to capture perspectives from youth participants, parents and caregivers, and community members. Qualitative tools to be used include in-depth interviews, focus group discussions, and participant and facilitator observations. The mixed-method evaluation design is detailed in Textbox 2.

Data collection methods.
**QUALITATIVE METHODS**

**Adolescent**
In-depth interviewsFocus group discussionsSession materialsParent-youth workbook
**Parent**
In-depth interviews (pre- & post-intervention)Parent session materials
**Facilitator**
Session debrief reflectionsChallenges, solutions, and adaptation logsIn-depth interviews
**Participant and facilitator observations**

**QUANTITATIVE METHODS**

**Adolescent Survey**
Sociodemographic informationSocial and emotional mindsets and skillsDiscrete choice experimentParent-youth workbook

#### Youth Surveys

The evaluation surveys for youth in *Discover* have been developed following a review of existing, validated tools that have been previously used in similar low-resource settings and tested through multiple pilot field tests with young adolescents in study sites. The surveys have been adapted through an iterative process following the pilot intervention and through meetings with Tanzanian and US research evaluation team members. Some of the measures that have been adapted include the following: gender equality—Gender Roles, Equality and Transformations [34]; curiosity—the Trait State Curiosity Scale [35]; empathy—the Empathy Questionnaire for Children and Adolescents [36]; growth mindset—Dweck Growth Mindset Questions [37]; and technology use and uptake—Media and Technology Usage and Attitudes Scale [38].

Final survey measures have been reviewed for relevance, cultural meaning, and acceptability by youth. Following this, the survey will be transferred to a tablet-based questionnaire for use in one-on-one interviews. The survey will be translated and back-translated from English to Swahili. The final *Discover* measures are listed in Multimedia Appendix 3.

#### Discrete Choice Experiment

We have developed a discrete choice experiment to assess adolescents’ gender perceptions, attitudes, and roles. This is a quantitative technique for eliciting individual preferences and hence informing policy, planning, and resource allocation decisions [39]. Typically, in a discrete choice experiment, study participants are repeatedly presented with scenarios on several attributes and asked to state their preference. In our approach, adolescents will be presented with 3-5 scenarios under each attribute and asked to decide whether the scenarios best describe boys, girls, or both boys and girls. The attributes will complement the social and emotional mindsets and skills from our intervention modules. Response options will be presented as cartoon images of boys only, girls only, or both girls and boys; participants will have to pick one image for each scenario.

#### Qualitative Data Collection

In-depth interviews with youth and parents will be conducted at the start of the program over a period of 6 weeks. Interviews with youth will be conducted by trained qualitative researchers after school hours. Parent interviews will be conducted over the phone at a time preferred by the parent. During classroom sessions, trained observers will keep notes of youth and facilitator engagements. This will be done throughout the project. Upon completion of the project, endline in-depth interviews with youth and parents lasting approximately 30 minutes will be conducted. In-depth interviews will be conducted with all facilitators. Further, focus group discussions will be held with groups of 4-6 youth, and in-depth interviews with teachers will be completed. Recordings of all interviews and focus groups will be transcribed in Swahili and then translated to English by project staff.

### Sample Size and Power

The sample size of 579 was chosen to be able to measure the minimum detectable effect of the *Discover* intervention on outcomes of social and emotional mindsets and skills. A sample of 186 students per study group produces an effect size of 0.28 and 80% power, assuming a 1-sided *t* test and α level of .05 to allow for multiple testing across groups. Randomization will be done at the individual level because the research protocol poses minimal risk for contamination. The project does not have a prior estimate of the intracluster correlation coefficient between individuals nested within a school, so we have used 0.39, adapted from similar studies on social and emotional interventions in sub-Saharan Africa [40]. The control groups (A and B) will each have 186 students, and the remaining participants will be in the treatment group (Group C).

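### The minimum detectable effect of 0.28 does not follow from the stated inputs, which give 0.26, and the ICC of 0.39 said to have been used does not reconcile with it

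*Protocol article*

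**What the plan says.** All the planning inputs stand in one paragraph of the protocol article, under Sample Size and Power.

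- Size, effect and power: "A sample of 186 students per study group produces an effect size of 0.28 and 80% power".
- Test: "assuming a 1-sided *t* test".
- Significance level: "α level of .05 to allow for multiple testing across groups".
- Unit of allocation: "Randomization will be done at the individual level because the research protocol poses minimal risk for contamination".
- ICC for individuals within a school, for which the project had no estimate of its own: "so we have used 0.39, adapted from similar studies on social and emotional interventions in sub-Saharan Africa".
- Group sizes: "The control groups (A and B) will each have 186 students", with the remainder of the 579 in Group C, that is 579 − 2 × 186 = 207. Table 1 lists 186, 185 and 208, which changes nothing material below.

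The Randomization Procedure section describes a draw held at each of the four schools, so every school contributes children to all three groups. The paragraph gives no loss allowance, no divided alpha and no formula showing where the ICC entered.

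**The concern.** A two-sample t test needs only group sizes, alpha, sidedness and power to fix the standardised MDE. The article supplies all of these and then reports an MDE that differs from the one they imply. It adds an ICC that would normally move the MDE a long way in one direction or the other, yet the reported figure sits close to the value with no ICC at all. It also describes an undivided alpha as an allowance for multiple testing.

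This is the only power statement in the article. Readers will judge null or small effects against 0.28 without knowing which test, which analysed sample or which clustering assumption lies behind it.

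**Working it through.** **Method.** With SD = 1, MDE = (z for alpha + z for power) × √(1/n1 + 1/n2). Results were checked with the exact noncentral t.

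**1. The plan's own figure, from its stated inputs.** One-sided .05 gives z = 1.645, and 80% power gives z = 0.842; the sum is 2.4865.

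- 186 versus 186: √(2/186) = 0.1037, so MDE = 2.4865 × 0.1037 = **0.258** (exact t 0.258).
- 186 versus 207: √(1/186 + 1/207) = 0.1010, so MDE = 0.251 (exact t **0.252**).
- Power at 0.28 with 186 per group: 0.28/0.1037 = 2.700; 2.700 − 1.645 = 1.055; Φ(1.055) = **85.4%** (exact t 85.3%), against the stated 80%.
- n per group needed for 0.28: 2 × (2.4865/0.28)² = 157.7, so 158 (159 by exact t), against 186.

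The stated 0.28 is not reproduced.

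**2. Inputs that do reach about 0.28.** Each needs something the text does not state or contradicts.

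| Reading | MDE | Conflict with the text |
|---|---|---|
| One-sided .05, 15% loss (158/0.85 = 186) | 0.28 | no loss allowance stated |
| One-sided .05, 500/579 retained (186 × 0.864 = 160.6, about 161 per group) | 0.278 | same |
| Two-sided .05, 186 vs 207 or 208 | 0.283–0.284 | text says one-sided |
| Two-sided .05/3, A and B pooled vs C | 0.280–0.281 | text gives 186 per group, one-sided, undivided alpha |

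Two-sided .05 with 186 versus 186 gives 0.291.

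**3. The ICC of 0.39.** The starting point is 0.258.

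- *School design effect.* 186/4 = 46.5 children per group per school. 1 + 45.5 × 0.39 = 18.7; effective n = 186/18.7 = 9.9; MDE = 0.258 × √18.7 = **1.12**.
- *School variance removed by blocking.* 0.258 × √(1 − 0.39) = **0.20**.
- *Delivery groups, sizes from Table 1.* For 4–5 children the design effect is 2.17–2.56 and the MDE 0.38–0.41. For 15–26 children it is 6.46–10.75 and the MDE 0.66–0.85.

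None gives 0.28. As a school design effect, the ICC that turns 0.258 into 0.28 is ((0.28/0.258)² − 1)/45.5, about 0.004, roughly a hundredth of 0.39. Two less usual readings come near. Blocking with t quantiles on 3 df gives 0.27. Reading 0.39 as a baseline-to-follow-up correlation, with one-sided .05/3, gives 0.284, but the text calls 0.39 an intracluster correlation and does not divide alpha.

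**4. Multiplicity.** The number of comparisons is not stated, so a range is shown. For 186 versus 186, one-sided, exact t:

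- undivided .05: 0.258
- .05/2 (two comparisons): 0.291
- .05/3 (three comparisons): 0.309

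The stated alpha is the undivided one.

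**The case against.** **Attrition may explain the figure.** The Results section expects 500 of the same participants in the second phase. At that retention the stated one-sided test gives 0.278, which rounds to 0.28. A condensed article may leave a loss allowance to the full protocol. This stands as a plausible explanation, so it would be wrong to say that 0.28 cannot be tied to the stated test. But the article attaches 0.28 to 186 per group without qualification and does not link the 500 to the sample size.

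**The error is conservative.** This also stands. Before clustering and loss, the stated design detects a smaller effect than claimed, and the gap is about 0.02 SD. A reader might infer from the 1.12 that the trial is badly underpowered. The documents do not support that, because allocation is within school and a school-level design effect does not apply. The 1.12 shows only that 0.39 did not enter in that way.

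**An ICC can enter an individually randomised design.** A reader might infer that individual randomisation by itself rules out any use of 0.39. That is too strong, since blocking by school and clustering by delivery group are legitimate routes. The objection to 0.39 is numerical: the conventional uses tried do not give 0.28, and the text does not say which was meant.

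**A two-sided test was perhaps intended.** The Group A versus Group C comparison fits at 0.28. The article says one-sided, however, and a match on the number does not establish a different test.

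**Conclusion.** The point holds as a reporting error in the trial's only stated power figure. On the stated inputs the MDE is 0.258 (0.252 against Group C) and power at 0.28 is 85%. This assumes a standardised outcome, no loss and independent observations. The statement that an ICC of 0.39 was used does not reconcile with 0.28 under any conventional use tried, and the multiplicity wording describes an allowance that the stated alpha does not make.

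The size is modest: 0.02 SD, in the conservative direction, before loss and delivery-group clustering. Both of those would raise the MDE. The article gives no ICC for delivery groups, so the net figure cannot be settled from it. Nothing here shows that the sample is too small, or which of the candidate explanations is the true one.

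**What to change.** Rewrite the one paragraph so that the test, group sizes, loss and clustering match the figure.

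- **MDE.** For the stated one-sided .05 test at 80% power, give 0.26 SD (186 vs 186) and 0.25 SD (186 vs 207), before loss and delivery-group clustering.
- **If 0.28 was meant to include loss,** state the allowance: about 15%, or 500 of 579 retained, which gives 0.278 at 161 per group.
- **If a two-sided test was intended,** say so and give 0.28 (A vs C) and 0.29 (A vs B).
- **ICC.** Delete the statement that 0.39 was used unless it entered the calculation. If it did, give the formula and the resulting MDE.
- **Multiplicity.** Remove the claim that alpha .05 allows for multiple testing, or state the divided alpha, the number of comparisons and the matching MDE.

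The sponsor should confirm what was actually calculated before choosing among these. The cost is wording only. Enrolment for the first phase was complete when the article was written, and no change to the sample is implied. Under the stated one-sided test with no loss or division of alpha, the corrected figure is slightly more favourable than the published one; it becomes less favourable if alpha is divided or clustering is added.

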### Overview of Discover Learning Project

The primary aim of the Discover Learning Project (*Discover*) is to test an intervention for very young adolescents to promote positive social and emotional skills and mindsets that have the potential to transform gender norms and attitudes. A secondary aim is to better identify effective components of *Discover* that are scalable and require the fewest resources to implement. The study aims are detailed in Textbox 1.

*Discover* study design.

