### Intervention Components

The intervention design focuses primarily on increasing positive gender norms and boosting the outcome of each social and emotional mindset and skill among study participants. The intervention includes the following elements.

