### Data Analysis

Quantitative statistical data analysis will be conducted using Stata SE 16.0 (StataCorp). For each group, we will test using an intent-to-treat model to determine the effectiveness of each group on (1) social and emotional mindsets and skills outcomes (curiosity, generosity, persistence, purpose, growth mindset, and prosocial behavior) and (2) gender norms, attitudes, and beliefs. Descriptive statistics will be calculated for each measure per intervention group and will be used to check for skewness and data non-normality. The psychometric properties of each measure will be assessed using confirmatory factor analysis to assess the adequacy of factor structures suggested by previous studies. Additional analyses will be conducted using *t* tests and logistic regressions to explore potential confounders of these relationships such as age, gender, and assigned facilitator. Validated measures will be used for structural equation modelling to test the relationships between intervention groups on social, emotional, and identity learning measures. For each model tested, structural equation modelling will be used to test (1) overall fit, (2) the significance of structural paths, and (3) the amount of variability of the latent variables accounted for by observed variables. Model fit will be assessed by using goodness-of-fit indices including the chi-square, the root mean square error of approximation [41], the comparative fit index [42], the Tucker-Lewis index [43], and the standardized root mean residual.

Qualitative data analysis will be conducted in ATLAS.ti (ATLAS.ti Scientific Software Development GmbH). After completion of interviews and focus groups, a Tanzanian translator will complete translation from Swahili to English. The translations will be cross-checked by researchers in Tanzania. Transcripts will be coded using grounded theory methodology, and content analysis will be performed to identify key themes. Quotes will be selected as exemplars of these themes. Additional qualitative materials include participant observations, facilitator debrief reflections, parent session notes, and teacher interviews. Each of these documents will be translated from Swahili to English by the research team and summarized, and key themes will be extracted. Artifacts from youth will be collected throughout the intervention implementation to serve as exemplars of curriculum implementation.

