## Discussion

Findings from *Discover* will provide evidence of the impact of the different components of a developmentally informed social, emotional, and identity learning intervention for very young adolescents by comparing outcomes in groups A, B, and C and emergent themes from interviews and focus groups. Synthesis of quantitative and qualitative results will allow for identification of the highest impact components and resources required for the intervention. Results from structural equation modelling will be used to create a testable model of the relationships between social, emotional, and identity development on gender equity outcomes. These results will be used to develop a scalable, low-resource intervention program. This study tests the translation of developmental science principles to youth programs. In addition, findings have the potential to be replicated in other low-resource contexts. This study has some limitations. Randomization of adolescents will be done at the individual level and not the school level to maximize participation. Findings from the intervention will therefore apply to the individual level but cannot be extrapolated to the community level. Despite efforts to ensure intervention groups receive the package of components pertinent to that group, there is a possibility that some adolescents will discuss their group’s activities with friends and siblings, and therefore groups may become aware of intervention components received by other groups. The findings from this study will contribute to the evidence base on development science for very young adolescents. Further, the study design, methods, and evaluation will be useful for other studies that are invested in gender-transformative interventions through support of social and emotional learning. *Discover* will identify the impact of different intervention components that can be leveraged to replicate and scale up similar programs in peri-urban, low-resource settings.

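### An undivided one-sided 5% test is presented as an allowance for multiple testing, which it is not, and the stated sample size does not fit that alpha

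*Protocol article*

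**What the plan says.** Sample Size and Power states the calculation as "A sample of 186 students per study group produces an effect size of 0.28 and 80% power". The sidedness is one-sided and the alpha is .05, undivided. The same sentence gives the reason for that alpha: "α level of .05 to allow for multiple testing across groups". No divided alpha or other correction appears there.

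Data Analysis plans an intent-to-treat test to "determine the effectiveness of each group on (1) social and emotional mindsets and skills outcomes". It names six such outcomes and adds gender norms, attitudes and beliefs. The Discussion says the components will be judged "by comparing outcomes in groups A, B, and C". The article does not single out one outcome or one contrast as the lead test.

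Table 1 gives 186, 185 and 208 participants in groups A, B and C. The text gives 186 each in A and B, which leaves 579 − 372 = 207 for C. That difference of one is immaterial here.

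**The concern.** A multiplicity allowance has to tighten the threshold for each test. The stated choice does the reverse. One-sided .05 uses a critical value of 1.645, which is the two-sided .10 cut-off, and nothing is divided across the three arms. A reader would take from the sentence that the error rate across groups is controlled, when the sentence provides no control.

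The trial is meant to identify which components have the highest impact and should be scaled up, and a false positive in one outcome and one arm pair would distort that choice. According to the Results section, phase I follow-up data were collected in October and November 2019 and analysis was unfinished when the article was written. A lead test named after that could be influenced by the data.

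**Working it through.** **Inputs.** From Sample Size and Power: 186 per group, standardised effect 0.28 (SD = 1), 80% power, one-sided alpha .05. From Table 1: 186/185/208. From Data Analysis: six named outcomes plus at least one for gender norms, so at least seven. From the Discussion: three arms compared, giving two contrasts (C–A, C–B) or three (adding B–A). The test count is inferred, not stated.

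**1. The plan's own figure.** n per group = 2(z₁₋α + z₀.₈)²/d².
- One-sided .05: 2(1.645 + 0.842)²/0.28² ≈ 158. The exact t calculation gives 158.4, so 159. The stated 186 is not reproduced.
- Power at 186 versus 186 with d = 0.28: 85.4%.
- Minimum detectable effect = (z₁₋α + z₀.₈)·√(1/n₁ + 1/n₂). At 186 versus 186: 2.487 × √(2/186) = 0.258. At 186 versus 208: 2.487 × √(1/186 + 1/208) = 0.251.

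**2. What might explain 186 and 0.28.**
- One-sided .025 (equal to two-sided .05) at 186 versus 208: 2.802 × √(1/186 + 1/208) = 0.283, with 79.2% power at 0.28. This is close to the stated pair, and .025 is .05 split over two contrasts.
- Alternatively, 158/(1 − 0.15) = 186, that is, the stated inputs plus 15% dropout. The article mentions no dropout allowance.

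Neither is stated, so the alpha actually used cannot be determined from the article.

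**3. Error rate if one-sided .05 is applied as written.** With independent tests the chance of at least one false positive is 1 − 0.95^m: 30.2% for m = 7, 51.2% for m = 14, 65.9% for m = 21. Contrasts that share an arm are not independent, so 100,000 null trials were simulated with arm sizes 186/185/208, seven outcomes and a common inter-outcome correlation (assumed, as the article gives none). A test counted as positive when z > 1.645.

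| Contrasts | corr. 0 | corr. 0.3 | corr. 0.5 |
|---|---|---|---|
| C–A only | 30% | 24% | 20% |
| C–A, C–B | 48% | 39% | 33% |
| C–A, C–B, B–A | 61% | 52% | 45% |

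One outcome with three contrasts gives about 12.5%.

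**4. How much is due to one-sidedness?** Ordinary two-sided .05, counting false positives in either direction, gives 49/45/39% for two contrasts and 60/55/47% for three. The totals are nearly the same, so the number of tests drives them. Counting only false benefits, two-sided .05 (one-sided .025) gives 28/23/20% and 38/32/28%. One-sidedness therefore adds false claims of benefit on top of an inflation that is already there.

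**5. After the change to two-sided .05.** Minimum detectable effect for C (208) versus A (186): 0.283. For A versus B at 186 each: 2.802 × √(2/186) = 0.291.

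**The case against.** The clause is a sample-size assumption. Data Analysis fixes no alpha or sidedness, and it also plans structural equation models, so a count of 14 or 21 pairwise tests is an inference. Adjustment procedures and testing order often belong in an analysis plan, and none is shown here. This stands as far as it goes: the lack of a full multiplicity scheme is not itself the fault. It does not rescue the sentence, because no later document can make an undivided one-sided .05 into an allowance for multiple testing.

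The sentence may also just misreport a calculation done at one-sided .025. That is possible, but it would cover two contrasts on one outcome only. Seven outcomes at that level would still give about 20–28% for two contrasts and 28–38% for three.

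A reader might infer more than the documents support in three ways.
- That one-sidedness makes a false positive likely. Two-sided .05 gives nearly the same any-direction rates, and the chance passes 50% only with three contrasts and outcome correlation up to about 0.3.
- That different sections declare rival primary outcomes. The Overview says the primary aim "is to test an intervention for very young adolescents to promote positive social and emotional skills and mindsets" and links these to gender norms. Intervention Components says "The intervention design focuses primarily on increasing positive gender norms", but that describes the emphasis of the design, and the same sentence goes on to include each mindset and skill. Textbox 1 lists research aims without calling them primary outcomes.
- That a one-sided test would hide harm from mixed-gender sessions. Table 1 gives mixed-gender groups to all three arms, so no arm contrast of either sidedness isolates that effect.

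**Conclusion.** The point holds. The stated reason for the alpha is false: one-sided .05 gives no multiplicity protection and doubles the error in the direction of benefit (5% against 2.5%). The sentence is also inconsistent with its own numbers (about 159 per group needed, or 85% power at 186), so either the alpha or another input is misreported.

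The error-rate range of about 20% to 61% is conditional. It assumes no true effects, no correction elsewhere, one phase of testing, at least seven outcomes tested pairwise, and inter-outcome correlation between 0 and 0.5. It should be reported as a range, with the number of uncorrected tests named as the main cause.

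**What to change.** In Sample Size and Power, delete the clause that offers the alpha as a multiplicity allowance, and state the alpha and sidedness actually used. Adopt two-sided 5% tests. Restate the minimum detectable effect on the article's own method, without clustering or dropout, as 0.283 for C (208) versus A (186) and 0.291 for A versus B.

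Name one primary outcome and one lead contrast. One workable order is C versus A, then C versus B, then B versus A in fixed sequence, which needs no split of alpha. Treat the other outcomes as secondary, with Holm adjustment. The sponsor may prefer another lead contrast; what matters is that it is fixed.

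Set and date this before any outcome comparison is seen. If comparisons have already been seen, say that the choice was made afterwards.

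No additional participants are needed. The cost is a less favourable minimum detectable effect than the stated one-sided test would give (0.251 to 0.283 for C versus A, 0.258 to 0.291 for A versus B), and fewer secondary results will be called significant.

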### Research Team Training

Core research team members will complete training on research ethics prior to the study. Their training will include confidential handling of data, obtaining consent and assent from study participants, and data collection and management. The field research team will be composed of 2 master trainers and 12 community facilitators. Training will be conducted in two phases. First, the master trainers will be trained over two weeks by the *Discover* Project Manager. The training will cover research ethics, gender-transformative content, technology use, and partnering with the community. Second, community facilitators will be trained with support from the master trainers over eight days. During the training, 6 facilitation principles will be adapted to facilitate discovery learning. They are (1) scaffolding learning to create a safe space for learners, (2) emphasis on learning over education, (3) withholding judgment since learning is a nonlinear process, (4) encouraging teamwork and positive group dynamics, (5) disrupting gender norms, and (6) encouraging a growth mindset. Sessions will use a combination of presentations, discussion, practice, and reflection.

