### Randomization Procedure

Participating 10- to 11-year-olds from grades 3, 4, and 5 will be identified from each school. At each school, we will hold an event where we line up eligible youth outside their classrooms. A research assistant will hold a box with pencil sharpeners of different colors inside. The box will have a small hole large enough to fit a hand through but small enough that students cannot see the pencil sharpeners. Each youth will select one sharpener at random. Students will be assigned to groups A, B, or C depending on whether they pick pink, yellow, or blue pencil sharpeners, respectively. Youth will then be matched to their selected pencil sharpener with a research assistant holding the same color, and that research assistant will register students to the assigned group. Table 1 lists the expected results of randomization to the three groups, according to the sample size calculation, and the intervention components that will be administered to each group.

**Table 1 table1:** Intervention components offered per study arm.

Study components	Group A (n=186)	Group B (n=185)	Group C (n=208)
Number of sessions	6	6	18
Ubongo Kids videos	✓	✓	✓
Mixed gender groups of size	15-26	4-5	4-5
Discussion and activities	✗	Self-guided	Guided by trained facilitators
Parent-child workbook	✗	✗	✓

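### Treatment is delivered in groups whose size differs by arm, but the power statement considers only school clustering and the named analyses have no term for delivery group, so standard errors are too small if children within a group are correlated

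*Protocol article*

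**What the plan says.** All references are to the Methods section of the Protocol article.

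- **Randomization Procedure.** At each school, every eligible child draws a colour that assigns A, B or C, so each school contains all three arms. Table 1 gives 186, 185 and 208 children. Its row "Mixed gender groups of size" shows 15-26 for A and 4-5 for B and C. Its row on discussion and activities shows none for A, self-guided for B, and "Guided by trained facilitators" for C.
- **Research Team Training.** "The field research team will be composed of 2 master trainers and 12 community facilitators".
- **Sample Size and Power.** The power claim is "A sample of 186 students per study group produces an effect size of 0.28 and 80% power". It rests on a one-sided t test at the 5% level. On clustering: "The project does not have a prior estimate of the intracluster correlation coefficient between individuals nested within a school". A value of 0.39 is therefore borrowed from other studies. No ICC or design effect is given for session group or facilitator.
- **Data Analysis.** The effect analysis is an intent-to-treat model, not further described, and "structural equation modelling to test the relationships between intervention groups". The t tests and logistic regressions are additional analyses to explore confounders, and assigned facilitator is one of the confounders listed. No random effect, multilevel term or cluster-robust standard error is named.

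**The concern.** This is an individually randomised trial with group-delivered treatment. Randomisation makes children independent at baseline, but afterwards those in B and C work in shared teams, and in C also under shared facilitators. The article's hypothesis is that learning in small mixed-gender groups produces the change, so outcomes within a delivery group can be expected to correlate.

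A school effect is common to all arms and largely cancels from an arm contrast. A delivery-group or facilitator effect belongs to one arm only and does not cancel. The plan therefore considers clustering at the level that matters least for the comparison and omits the level that matters.

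At stake are the width of the confidence intervals and the type I error. Because group size differs by arm, the understatement differs between C vs A and C vs B. That is awkward in a trial meant to compare the components of the package.

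**Working it through.** **Inputs from the article.** n = 186 (A), 185 (B), 208 (C); effect 0.28 SD; one-sided 5%; group sizes 15-26 (A) and 4-5 (B, C); 12 facilitators.

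**Assumptions.** Mean group size 20.5 in A and 4.5 in B and C (midpoints). Delivery-group ICC of 0.02, 0.05 or 0.10, since the article gives none. Normal approximation, all children analysed.

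**Step 1: the plan's own figure.** With 186 vs 186 and independent children, the minimum detectable effect (MDE) is (1.645 + 0.842) × √(2/186) = 0.258, and power for 0.28 is 85.4%. The stated 0.28 at 80% is not recovered from the stated inputs. The school ICC does not explain the gap: with 186/4 = 46.5 children per school and arm, the design effect would be 1 + 45.5 × 0.39 = 18.7 and the MDE about 1.12. With the Table 1 sizes, C vs A has 87.1% power if children are independent.

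**Step 2: formulas for an arm contrast.**

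- True variance: V = [1 + (m₁ − 1)ρ₁]/n₁ + [1 + (m₂ − 1)ρ₂]/n₂
- Naive variance: V₀ = 1/n₁ + 1/n₂
- Actual one-sided error: 1 − Φ(1.645 × √(V₀/V))
- Power: Φ(0.28/√V − 1.645)
- MDE: 2.486 × √V

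**Step 3: C vs A, same ICC in both arms.** At 0.05, V = 1.175/208 + 1.975/186 = 0.01627, against V₀ = 0.01018. The ratio of standard errors is √(0.01627/0.01018) = 1.26.

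| ICC | True SE / naive SE | Naive SE too small by | Error | Power | MDE |
|---|---|---|---|---|---|
| 0.02 | 1.11 | 10% | 7.0% | 80% | 0.28 |
| 0.05 | 1.26 | 21% | 9.7% | 71% | 0.32 |
| 0.10 | 1.48 | 32% | 13.3% | 59% | 0.37 |

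Over the stated ranges of group size, power at 0.05 is 67-75%.

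**Step 4: C vs A, no clustering in A.** Group A has no discussion or activities, so zero is a lower bound there. At 0.05 in C teams, V = 1.175/208 + 1/186 = 0.01103.

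| ICC in C (A = 0) | Error | Power |
|---|---|---|
| 0.02 | 5.3% | 86% |
| 0.05 | 5.7% | 85% |
| 0.10 | 6.4% | 82% |

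**Step 5: C vs B, teams of 4.5 in both.** At 0.05, V = 1.175/208 + 1.175/185 = 0.01200; error is 6.5% and power 82%.

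**Step 6: facilitator as the cluster in C.** If all 12 serve C, each has about 208/12 ≈ 17 children. At an equal ICC of 0.05, C vs A has 11.6% error and 64% power; with no clustering in A, error is 8.1%.

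**Step 7: where power crosses 80%.** With teams as the cluster in C, setting power to 0.80 and solving for an equal ICC gives about 0.02 for C vs A and 0.07 for C vs B.

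**The case against.** The strongest objection concerns size. The large figures come from giving A, with its groups of 15-26, the same ICC as C. Yet A only watches videos, and the mechanism that would create correlation is discussion and teamwork. With zero in A the inflation is small (Step 4). This stands. Zero is a lower bound, because shared viewing may still create some correlation, so Steps 3 and 4 should be read as a range.

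Second, the article is condensed. Variance structure is often left to a fuller analysis plan, the intent-to-treat model is not described, and facilitator is at least named as a variable. This stands in part: independence in the analysis is inferred from the methods listed. The Sample Size and Power section, however, is not silent. It addresses clustering and fixes it at school level. Exploring facilitator as a confounder does not correct a standard error, and it does not cover the groups in A or the self-guided teams in B.

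Third, the article does not say that all 12 facilitators serve C, nor that team membership stays fixed across sessions. Both points stand, so Step 6 is illustrative.

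A reader might infer that the trial is underpowered outright, or that the comparison of arms is biased. The documents support neither. The stated inputs leave slack above 80%, and whether clustering uses it up depends on an ICC that is not given. The problem lies in the standard errors; the effect estimates are not biased by it.

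**Conclusion.** The point holds. The plan considers clustering at school level, which is crossed with arm, and names no term for delivery group or facilitator. Analysed that way, any positive within-group correlation gives standard errors that are too small and a type I error above nominal, more so for contrasts involving A if A's viewing groups are themselves correlated.

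The size is conditional. For C vs A over ICCs of 0.02 to 0.10, the actual error of a nominal one-sided 5% test is 7.0-13.3% if A shares the ICC and 5.3-6.4% if A has none. For C vs B at 0.05 it is 6.5%. Clustering in C by facilitator would be worse.

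Whether power falls short of the stated 80% is also conditional. With teams as the cluster in C and all children analysed, it takes an equal ICC above about 0.02 for C vs A or 0.07 for C vs B. If the slack in the sample size was meant for attrition, which the section does not state, the thresholds would be lower.

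**What to change.** 1. Retain the delivery-group ID (viewing group in A, team in B and C) and the facilitator ID for every child.
2. Estimate the arm effects with a mixed model that has arm-specific random effects for delivery group, and for facilitator in C, adjusts for school, and uses small-sample degrees of freedom (Satterthwaite or Kenward-Roger).
3. In the structural equation models, use standard errors clustered on delivery group or facilitator.
4. In Sample Size and Power, replace the school ICC with a range of arm-specific delivery-group ICCs and restate the MDE under the protocol's own one-sided test. For C vs A with equal ICCs of 0.02, 0.05 and 0.10 it is 0.28, 0.32 and 0.37. Show the case of little or no clustering in A beside it.

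The cost is a retained identifier and some analysis wording. The downside is somewhat wider intervals and a less favourable MDE. The article reports that data analysis was not yet concluded when it was written, so the change could still be made before the results were fixed.
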